### Primary and secondary outcomes

The primary outcome is the feasibility of the whole intervention, defined by the following parameters:

- Adherence to treatment: to define that the patient completed the protocol, at least 75% of the planned sessions should be performed.- Retention: successful retention rate is reached if at least 75% of enrolled participants complete the prehabilitation program.- Adverse events: absence of any adverse event attributable to the prehabilitation program, except for expected transient mild symptoms previously reported for neuromodulation (headache, syncope, and skin irritation) or motor training (mild pain and fatigue).- Patient's satisfaction: At the end of the protocol, participants fill out questionnaires evaluating the patient's satisfaction with the treatments received (13).

Secondary outcomes are related to exploratory analyses of the effectiveness and potential mechanisms of action of the proposed intervention. We investigate changes from baseline regarding clinical outcomes, fMRI, and TMS mapping. Notably, the goal of the intervention is to reduce the functional relevance of targeted areas because of compensatory activation of other brain resources within the same functional network. Slow-growing tumors already demonstrated that similar neuroplastic changes may occur, with the tumor mass progressively interfering with the functionality of critical areas, while remote brain areas increase their activation; such compensatory mechanisms may explain why these types of tumors are asymptomatic and without any functional deficits in the initial phases (14, 15). From this perspective, the prehabilitation program could be considered a method to artificially optimize and accelerate this neuroplastic adaptation for therapeutic purposes (3). Therefore, we do not expect significant changes regarding clinical outcomes, whereas we consider changes in neuroimaging and neurophysiology outcomes as indicators for the effectiveness of the prehabilitation program.

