#### Neuroimaging

Magnetic resonance imaging (MRI) is acquired to assess anatomical and functional (fMRI activation maps) brain changes due to intervention and surgery. For instance, the development of novel activation sites distant from the surgical target may indicate that NICP was effective in promoting a reduction of functional relevance for targeted areas, in favor of a more distributed network. Therefore, all patients undergo three identical MRI sessions: (1) before NICP, (2) after NICP but before surgery, and (3) after surgery. Each session consists of MRI data acquisition using a 3 Tesla Siemens PRISMA scanner and a 32-channel head coil. The protocol includes accelerated multiband sequences adapted from the Human Connectome Project and provided by the Center of Magnetic Resonance Research (CMRR) at the University of Minnesota.

Regarding anatomical acquisitions, a high-resolution T1-weighted structural image is obtained with a magnetization-prepared rapid acquisition gradient-echo (MPRAGE) three-dimensional protocol, in which in an ascending fashion a total of 208 contiguous axial slices are obtained [repetition time (TR) = 2400 ms, echo time (TE) = 2.22 ms, inversion time = 1000 ms, flip angle = 8°, field of view (FOV) = 256 mm and 0.8 mm isotropic voxel]. In the same session, a high-resolution multishell diffusion-weighted MRI scan is obtained. This scan consists of two multiband acquisitions (anterior–posterior; acceleration factor = 4), sensitized in 99 monopolar directions with a b-value of 3000 s/mm2 in an echo-planar imaging sequence [TR = 3230 ms, TE = 89.20 ms, section thickness = 1.5 mm, voxel size = 1.5 × 1.5 × 1.5 mm, FOV = 210 mm].

In terms of quantifying brain function, resting-state and task functional MRI (fMRI) are acquired. Both consist of high-resolution multiband (anterior–posterior phase-encoding, acceleration factor = 8) interleaved acquisitions [T2^*^-weighted EPI scans, TR = 800 ms, TE = 37 ms, 750 volumes, 72 slices, slice thickness = 2 mm, FOV = 208 mm]. First, resting-state fMRI is acquired while the patient is instructed to keep his eyes closed and remain still without falling asleep.

Then, task fMRI is acquired during three language and three motor paradigms, which adhere to the following procedures:

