#### Neurophysiological assessment

By performing neuronavigated TMS mapping, we compare the anatomical distribution of active targets pre- vs. post-intervention. The same targets and intensity of stimulation defined at baseline are used at the end of the intervention, to allow comparisons. A figure of 8 coil (MagPro Cool B65-AP-RO Coil) connected to a transcranial magnetic stimulator (MagVenture MagPro x100) is driven by a robotic arm (Axilum Robotics TMS-Cobot) controlled manually or through a dedicated neuronavigation software (Brainsight TMS neuronavigation). We apply biphasic current with an anterior–posterior followed by a posterior–anterior current direction in the brain; the TMS coil is held tangential to the scalp, the handle pointing backward with a 45-degree deviation from the sagittal plane. For curvilinear 3D brain reconstruction (MNI coordinates), participant's structural and functional MRI data are uploaded. Grids of targets (inter-target distance: 10 mm) are defined based on anatomical landmarks for the subsequent motor/language mapping protocol and to determine the hotspot for neuromodulation. Grids are placed in correspondence with the primary sensorimotor and premotor areas (motor mapping) and over the pars triangularis and the gyrus supramarginalis (language mapping).

The procedure for motor and language mapping (at baseline and at the end of the prehabilitation program) is as follows:

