For language mapping, a speech disruption protocol is applied. Initially, patients are familiarized with pictures and instructed to name them as soon as they appear on a screen in front of them. Once it is verified that the patient can name pictures correctly, we start language mapping. rTMS (five pulses at 5 Hertz, 90% RMT) is delivered to each target, together with presenting a picture on the screen (picture presentation time: 500 ms; delay picture-rTMS: 0 ms). The order of target stimulations and picture presentations is pseudo-randomized. An audio/video recording of the patient's response (from 0 to 3000 ms after the first rTMS stimulus) is evaluated offline by a neuropsychologist unaware of the target that has been stimulated to determine whether there was an episode of speech arrest, anomia, or other speech disruption phenomena. The language protocol is repeated until each target receives rTMS three times. A dedicated MATLAB script is developed to automatically synchronize rTMS with picture presentation and audio–video recording.

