### Statistical analysis

We use R software for statistical analysis and graphics (78). Given the small sample size (20 patients, based on a realistic estimate of the recruitment rate) and the use of ordinal scales, we perform non-parametric statistics. For descriptive reporting of continuous/ordinal variables, median and interquartile range (IQR) are used to indicate measures of central tendency and dispersion, respectively; frequencies are reported by indicating the absolute value, followed by the relative value (percentage) in brackets; in case of binary variables (such as gender), only one of the two variables is reported. For the primary analysis (feasibility), we report descriptively whether we met the criteria for recruitment, retention, and adverse events; adherence to treatment (both neuromodulation and behavioral training) is reported as the median (IQR). An exploratory analysis of effectiveness is conducted by performing a repeated-measure comparison (pre- vs. post-prehabilitation). Together with reporting the estimates of treatment effect, we indicate the actual level of significance (two-sided *p*-value) and 95% confidence interval (79). For quantitative and ordinal variables, we use Wilcoxon signed-rank test. For dichotomous variables, we use McNemar's test. For correlations between quantitative/ordinal variables measured at the same time point, we use Kendall's tau rank correlation coefficient. To explore prediction models, we use simple and multiple linear regression analyses for continuous/ordinal outcomes and simple and multiple logistic regression for binary outcomes. In case of missing data, we perform pairwise deletion. Further explorative analysis may include big data analysis of neuroimaging/neurophysiology data.

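### Map change is read as effectiveness without requiring that the same patient's trained function was preserved, so functional loss can add to the reported effect

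*Protocol article*

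**What the plan says.** Under Primary and secondary outcomes, the article states the aim: "the goal of the intervention is to reduce the functional relevance of targeted areas because of compensatory activation of other brain resources". The secondary outcomes are listed side by side: "We investigate changes from baseline regarding clinical outcomes, fMRI, and TMS mapping". It then says which of them speak to effectiveness: "we do not expect significant changes regarding clinical outcomes, whereas we consider changes in neuroimaging and neurophysiology outcomes as indicators for the effectiveness".

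Two later sections describe what a favourable change might look like. Neuroimaging offers, as an example, that "the development of novel activation sites distant from the surgical target may indicate that NICP was effective". Neurophysiological assessment says "we compare the anatomical distribution of active targets pre- vs. post-intervention", and fixes the conditions: "The same targets and intensity of stimulation defined at baseline are used at the end of the intervention, to allow comparisons".

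The Statistical analysis section gives the method: "An exploratory analysis of effectiveness is conducted by performing a repeated-measure comparison (pre- vs. post-prehabilitation"). Quantitative and ordinal variables get a Wilcoxon signed-rank test and dichotomous ones McNemar's test, with estimates, two-sided p-values and 95% confidence intervals. Kendall's tau is planned for variables taken at one time point. Regression models are mentioned without naming predictors or outcomes. Missing data are handled by pairwise deletion.

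**The concern.** The aim has two parts that must occur in the same patient: the target matters less, and other areas carry the function. A weaker response at the target fits that aim. It also fits a target that has stopped working with nothing taking over. The article itself notes that a growing tumour interferes with critical areas, and there is no control arm to show how much map change would occur without the intervention. The patient's own functional score is the most direct way to tell the two apart. It is measured before and after prehabilitation, but it is not part of the indicator and is not joined to the map result.

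At stake is the effectiveness statement in the results paper. A cohort map change plus a clinical test without significant change would be read as reorganisation with function preserved, although the two findings might come from different patients.

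**Working it through.** **1. Is there a within-patient link?** Going through the planned analyses:
- Wilcoxon and McNemar tests take one variable at a time across the cohort.
- Kendall's tau relates two variables at the same time point, not two changes.
- The regression sentence names no model of map change against functional change.
- Pairwise deletion allows the map test and the function test to rest on different patients.

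No link is stated.

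**2. Where can lost function look like the intended change?**
- *Motor TMS.* Mapping uses 120% of resting motor threshold and counts a response above 50 μV. Targets and intensity are held at baseline values, so a response lost through damage reads as an inactive target. No performance check is stated.
- *Task fMRI.* The task descriptions state no performance check. A patient who performs less can show less activation.
- *Language TMS.* "Once it is verified that the patient can name pictures correctly, we start language mapping". A patient who can no longer name would probably not be mapped and would leave the comparison. The loss is hidden but not scored as a gain.

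**3. Does the clinical test protect?** The plan's only design figure is n = 20, justified by the recruitment rate, so there is no power calculation to reproduce. Alpha is not stated; 0.05 is assumed. Suppose k patients decline and the rest are unchanged. With zero differences dropped, the exact two-sided signed-rank p is 2/2^k (exact McNemar gives the same value):

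| k of 20 | p, zeros dropped | p, Pratt (normal approximation) |
|---|---|---|
| 3 | 2/8 = 0.25 | 0.084 |
| 4 | 2/16 = 0.125 | 0.046 |
| 5 | 2/32 = 0.0625 | 0.026 |
| 6 | 2/64 = 0.031 | 0.015 |

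So up to 5 of 20 (25%) or, with Pratt's handling, 3 of 20 (15%) could decline without a significant result. With zeros dropped, p depends on k and not on n. Figure 1 ties the functional tests to the upper limb or the language/cognitive programme, so a given test may cover fewer than 20 patients, and the same k is then a larger share.

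Exact zeros are unlikely on timed tests, so a noisy version was simulated (exact test, n = 20, 4,000 runs). Assumptions: k patients lose 3 SD; the others have mean change 0, or a practice gain of 0.3 SD.

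| k | P(significant decline), no drift | with 0.3 SD practice gain |
|---|---|---|
| 3 | 12% | 1% |
| 5 | 33% | 6% |

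**4. What do the same patients do to the map test?** Assume the target response falls by 0.3 SD in the other patients and by 3 SD in the k patients. The chance of a significant reduction is 25% with k = 0, 51% with k = 3 and 74% with k = 5.

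**5. Joint illustration (assumed counts).** The target response falls in 15 of 20 (sign test p = 0.041), and 5 of those 15 decline in function. The other 15 of the 20 are functionally unchanged. Median functional change is 0 and p = 0.0625 with zeros dropped. Reduced target with function kept: 15 − 5 = 10 of 20, or 50% (exact 95% CI 27% to 73%).

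**6. Best case.** Even 0 declines in 20 leaves an upper two-sided 95% limit of 1 − 0.025^(1/20) = 16.8% for the decline rate.

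**The case against.** A reader might infer that the plan scores a patient with lost function as a success, or that it would report 75% where 50% is right. The article does not support that. It defines no responder and no success count; such a patient only adds to a cohort effect.

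A reader might also infer that the indicator is nothing more than a silent target. That is too strong. The imaging example concerns new distant activation, TMS compares the distribution of active targets, and both hemispheres are mapped. A silent target with nothing new elsewhere does not match the example. It is still only an example, so compensation is looked for but not required.

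Other safeguards are real but partial. The naming check covers language TMS only. A functional loss attributable to the programme fails a feasibility criterion, but a loss from progression does not. Post-surgical neurological status and the planned case-report database may reveal individual losses, yet neither changes what is read as effectiveness. Estimates and confidence intervals are promised along with p-values, but they too summarise the cohort.

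The numerical cases are constructed. Losing function in 25% of patients within 10 to 20 sessions may be pessimistic, and the limit depends on how zeros are treated.

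Finally, responder definitions for exploratory outcomes are often left to an analysis plan. That excuses a missing threshold. It does not cover the article's own choice of imaging and neurophysiology as the indicators of effectiveness, with function left out.

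**Conclusion.** The concern holds in limited form. The stated indicators of effectiveness do not include function, and the stated analyses do not join map and function within a patient. Loss of function can therefore enlarge the effect read as effectiveness, mainly through motor TMS and task fMRI. A non-significant clinical test is weak evidence of preservation: 5 decliners of 20 (3 with Pratt's handling) would pass at an assumed 0.05. The decline rates and effect sizes are assumptions, because the documents give none; the conclusion about the missing link does not depend on them. The outcome is secondary and exploratory, so the primary feasibility outcome is not affected. What the trial may say about effectiveness is.

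**What to change.** In Primary and secondary outcomes and in Statistical analysis, state that map change is read as evidence of effectiveness only where the same patient's trained function (upper limb, language or cognitive) did not decline from before to after prehabilitation.

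Add one per-patient table from data already scheduled in Figure 1 (maps at t0 and t4, function at t1 and t4):
- Cross reduced response at the stimulated target or targets (yes/no) with trained function kept (yes/no). The plural covers tDCS over distributed areas.
- Show new or increased activation elsewhere in the network alongside, since compensation is the stated mechanism.
- Give the count meeting both conditions with an exact 95% CI.
- List patients with target reduction and functional decline separately, not as evidence of effectiveness. Identify patients who could not be mapped afterwards, so that they do not vanish by deletion.

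The cost is some wording and one table, with no new data and no change to treatment. A decline threshold must be fixed in advance for one key test per programme, and the favourable count can only fall.

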#### Brain tumor classification and surgical outcomes

For oncological patients, tumor classification is based on the 2021 WHO Classification of Tumors of the Central Nervous System, which represents the most updated taxonomy of brain tumors, and the first classification system considering molecular profiling together with histology (16). Surgical outcomes consider results from intraoperative brain mapping, the absolute and relative amount of tumor removed, adverse events, and neurological status post-surgery.

#### Measurement of motor function, independency, and quality of life

Clinical assessments of upper limb motor function include the following measurements:

- Nine-Hole Peg Test (9HPT) evaluates manual dexterity (17, 18). A dedicated platform is placed in front of the patient, with nine pegs inside a container on the side to be evaluated, and nine holes on the other side. The patient is asked to place pegs into the holes and then put them back in the container, as fast as possible; they are allowed to perform a practice trial before the test trial. The therapist has a stopwatch to measure the time to complete the task and instructs the patient in case of errors (more than one peg picked up at the same time, pegs dropped on the table/floor, etc.). Excellent inter-rater and intra-rater reliability (19, 20) and sensitivity to change have been reported for patients with multiple sclerosis and other neurological disorders (20, 21).- Fugl–Meyer upper extremity (FM-UE) evaluates upper limb motor impairment, from reflex activity to voluntary motor control out of synergies (22). There are four separate sections, for the assessment of motor function at the level of the arm, the wrist, the hand, and speed–tremor coordination during a finger-to-nose task. Each item is scored as 0, 1, or 2, with a total score ranging from 0 to 66, with lower scores indicating more severe motor impairment. Excellent intra- and inter-rater reliability has been established (23), together with other psychometric measures related to validity, sensitivity, and responsiveness to change (24–26).- Shoulder abduction finger extension (SAFE) is a quick clinical assessment of upper limb strength, defined as the ability to perform abduction of the shoulder and extension of the index finger; it has potentially high prognostic value for neurological disorders, such as stroke (22). Scoring is usually based on the Medical Research Council scale, ranging from 0 (no visible muscle contraction) to 5 (normal). For the present study, we consider the corresponding items from FM-UE (27).- To quantify the strength of the hand grip, we use an electronic hand dynamometer. According to the standardized setup, patients are holding the dynamometer while sitting, shoulder adducted and neutrally rotated, elbow at 90-degree flexion, and forearm halfway between pronation and supination (28). They are asked to perform a maximal grip strength effort for 3 s, rest for 60 s, and then repeat the measurement two more times; the average of the three trials is used as the most reliable test result (29). Excellent test–retest reliability has been established (30).- Reaction time tasks are useful to measure the efficiency of basic processes for perception and response execution. For the present study, we use the Deary–Liewald reaction time task, a freely available program with established validity and reliability (31). In the simple reaction task paradigm, the patient is facing a blue computer screen with one white window in the center, and the index finger of the hand that is being evaluated over the space bar. The instruction is to click on the space bar as soon as an ‘X' appears on the white window; practice trials are allowed before the test trial, which consists of 20 stimuli with a random interval (1–3 s) in between. In the choice reaction task paradigm, there is a similar setup; this time there are four white windows aligned in the center of the screen, and the patient is holding the fingers over the four corresponding letters of the keyboard. Every stimulus consists of an “X” appearing randomly in one of the four windows; patients are instructed to click the corresponding letter as soon as possible. Practice trials are allowed before the formal test trial. For the present study, we adapted the program of reaction time tasks to evaluate one hand at a time without stringent time constraints.

For lower limb motor function, balance, mobility, independency, and quality of life, we consider the following measurements:

- Fugl–Meyer lower extremity: assessment of lower limb motor impairment (22). Each item is scored 0, 1, or 2, with a total score ranging from 0 to 34; low scores are indicative of more severe motor impairment. Excellent reliability has been established for the assessment of motor function after stroke (32).- Brunel balance assessment: assessment of balance based on 12-item hierarchical tasks, from sitting with arm support to stepping over a step, with excellent reliability and responsiveness to change (33).- Six-min walking test: submaximal test of aerobic capacity (34, 35). The patient is instructed to walk along a straight path for 6 min, with the goal of covering the longest distance possible within 6 min. Patients are allowed to walk, independently or with the use of assistive devices, and to take rests while standing. Running, sitting, or receiving physical assistance from the therapist (other than help for balance) is not allowed. For the present study, we use a 25-meter path, with visible turning points at the beginning and the end.- Dual-task assessment is performed, to investigate the interference between cognitive and motor tasks, in particular counting backward three by three during standing balance and gait.- Neurologic Assessment in Neuro-Oncology (NANO) scale, for the evaluation of neurological functional status in patients with brain tumor (36);- Karnofsky Performance Status (KPS), for the classification of oncological patients based on the severity of symptoms and their impact on functional independency (37).- EORTC-QLQ-C30: questionnaire of quality of life for oncological patients (38, 39).- BN20: EORTC brain cancer module, assessing quality of life specifically for patients with brain tumor (40).- FA12: EORTC module assessing the impact of fatigue on quality of life for oncological patients (41).

